*Tonic*	3. Emotional sharing will generally make sharers and supporters feel better, leading them to report positive mood changes. 4. Emotional sharing will generally help sharers to reappraise their feelings, leading them to report changes in emotional appraisals. 5. Compared to natural sharing, co-rumination may lead to equal or even more positive mood outcomes, possibly due to increased emotional closeness and perceived support. 6. Compared to natural sharing, co-rumination will be associated with smaller changes in emotional appraisals.
*Chronic*	7. Higher relationship quality and more constructive dyadic coping strategies will be associated with 1) stronger movement synchrony; 2) stronger cardiovascular synchrony; 3) stronger positive mood changes; 4) more emotional appraisal changes. 8. Higher relationship quality and constructive dyadic coping may buffer or attenuate potential differences between co-rumination and natural sharing in: (a) movement synchrony, (b) cardiovascular synchrony, (c) mood responses, and (d) emotional appraisal changes.

Moreover, we will conduct a series of exploratory analyses involving the secondary variables to further inform our understanding of interpersonal emotion regulation within close relationships. These exploratory analyses will probe the intricate connections between relational factors, individual characteristics, emotional sharing and physiological responses. In addition, in a second set of exploratory analysis we will be looking at synchrony in verbal communication: 1) linguistic synchrony; 2) vocal synchrony; 3) facial synchrony. These exploratory analyses are elaborated in Supplementary *1 in*
S1 File.

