#### Tonic timescale.

***Mood change analysis:*** To assess changes in mood over time (Hypothesis 3), we will use linear mixed-effects models (LMMs), treating time (pre vs. post) and condition (co-rumination vs. natural sharing) as fixed effects, and including random intercepts for participants nested within dyads to account for the non-independence of dyadic partners and repeated measurements. This approach enables us to examine overall mood changes without splitting sharers and supporters into separate analyses.

For Hypothesis 5, we will examine whether mood following co-rumination differs from mood following natural sharing using the same LMM framework, focusing on post-sharing mood scores across conditions.

***Emotional appraisal analysis:*** To evaluate changes in emotional appraisals (Hypothesis 4), we will calculate change scores by subtracting the pre-sharing appraisal rating from the post-sharing appraisal rating for each emotional episode. These change scores will then be entered into linear mixed-effects models, with condition as a fixed effect and random intercepts for participants nested within dyads. This approach accounts for within-person and within-dyad dependence and avoids the use of separate t-tests for each condition. Hypothesis 6 will be tested by comparing appraisal change scores between the co-rumination and natural sharing conditions using the same dyadic LMM framework.

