#### Chronic timescale.

***Relationship quality and dyadic coping analysis:*** We will employ regression analysis to examine the associations between relationship quality and dyadic coping strategies and movement and cardiovascular synchrony (*Hypothesis 7.1 and 7.2*). Additionally, to analyse whether dyadic coping and relationship quality are associated with mood changes we will add these variables as fixed factors in the linear mixed models built for testing hypothesis 3 on mood change over time (*Hypothesis 7.3*). Linear regression analyses will also be used to assess whether relationship quality and dyadic coping are related to emotional appraisal change (*Hypothesis 7.4*).

To assess whether co-rumination versus natural sharing influences the relationship between higher relationship quality and more constructive dyadic coping and movement and cardiovascular synchrony moderated regression analyses will be used (Hypotheses 8.1 and 8.2). To analyse whether the associations between relationship quality and dyadic coping with mood change are associated with effects of co-rumination versus natural sharing we will extend the linear mixed models used for testing hypothesis 7.3. The full model will consist of a random intercept for participants, fixed factors of assessment time and condition, their interaction, and mood as the dependent variable (*Hypothesis 8.3*). Moderated linear regression analyses will be used to assess whether better relationship quality and dyadic coping are associated with weaker effects of the co-rumination condition versus natural sharing on emotional appraisal change (*Hypothesis 8.4*).

The hypotheses presented in Table 1 and the data analysis techniques utilized constitute the core elements of our research. Additionally, we have identified and measured a range of secondary variables that could potentially influence these associations. Our aim is to incorporate these variables as covariates in the analyses to enhance our understanding of the findings. For all statistical tests α ≤ 0.05 (two-tailed) will be applied. Given the wide range of statistical tests performed, there is a concern regarding multiple comparisons. Therefore, to reduce the likelihood of Type I errors, we will apply the Bonferroni correction to all previously mentioned test results.

***Exploratory analyses summary:*** In our study, we plan to conduct exploratory analyses to investigate interpersonal synchrony in verbal communication:

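### The mood models stated for Hypotheses 7.3 and 8.3 name no interaction with relationship quality or dyadic coping, so no listed term carries either hypothesis

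*Protocol article*

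**What the plan says.** Table 1 lists the hypotheses as confirmatory. Under Hypothesis 7, higher relationship quality (RQ) and more constructive dyadic coping (DC) go with, among other outcomes, "3) stronger positive mood changes; 4) more emotional appraisal changes". Hypothesis 8 reads: "Higher relationship quality and constructive dyadic coping may buffer or attenuate potential differences between co-rumination and natural sharing", with mood responses as one of the outcomes.

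The base model is in the Tonic timescale section. For Hypothesis 3, mood is analysed in a linear mixed model "treating time (pre vs. post) and condition (co-rumination vs. natural sharing) as fixed effects", "including random intercepts for participants nested within dyads to account for the non-independence of dyadic partners".

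The Chronic timescale section builds on it. For 7.3, "we will add these variables as fixed factors in the linear mixed models built for testing hypothesis 3 on mood change over time". For 8.3, the authors say they will extend the 7.3 models and then list the result: "The full model will consist of a random intercept for participants, fixed factors of assessment time and condition, their interaction", with mood as the dependent variable. In the same paragraph, 8.1, 8.2 and 8.4 are each given a moderated regression.

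**The concern.** When the outcome is mood at each assessment, a predictor entered without a time interaction shifts the whole mood profile up or down. Its coefficient describes who is in a better mood on average, not whose mood improves. The quantity in Hypothesis 7.3 is the predictor x time term, which is not named.

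For 8.3 the quantity is the dependence of the condition difference on RQ or DC. The one interaction listed, time x condition, asks whether mood change differs by condition. That is nearer to Hypothesis 5.

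Two confirmatory results are at stake. Couples with a good relationship who merely start and finish in a better mood could be reported as support for 7.3. Hypothesis 8.3 could not be answered from the stated model, and interactions added after the data are seen would look data-driven.

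**Working it through.** **1. Terms needed against terms named**

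| Hypothesis | Quantity | Fixed terms named | Term carrying the hypothesis |
|---|---|---|---|
| 7.3 | Association of RQ, DC with mood change | time, condition, RQ, DC | RQ x time, DC x time: not named |
| 8.3 | RQ, DC moderating the condition difference | time, condition, time x condition (RQ, DC if carried over) | RQ, DC x condition after sharing: not named |

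The article has no figure of its own on this point to reproduce.

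**2. What the RQ main effect estimates**

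Table 2 places the mood checklist in the pre-sharing survey and the post-dialogue surveys, and there are four dialogues. That gives one pre and four post ratings per person. Let a be the slope of mood on RQ before sharing and b the additional slope after sharing, so that b is the effect on change. In a balanced random-intercept model the RQ coefficient is the slope of a person's mean rating:

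(1·a + 4·(a + b)) / 5 = a + 0.8b.

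It mixes level and change. If b = 0 and a is not zero, the test rejects for the wrong reason. If a = −0.8b, it misses a real change effect.

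**3. Illustrative size for 7.3**

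The documents give no variances. Assumed: SDs for dyad 0.4, person 0.6 and residual 0.7; RQ with SD 1 and partner correlation 0.5; 150 couples; no effect on change; dyad intercept included.

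- Total mood SD: √(0.16 + 0.36 + 0.49) = 1.005, so slopes are close to SD units.
- Variance of a person's mean about the dyad effect: 0.36 + 0.49/5 = 0.458.
- Information from dyad means: 150 × 0.75 / (0.16 + 0.458/2) = 150 × 0.75 / 0.389 = 289.2.
- Information from half-differences between partners: 150 × 0.25 / (0.458/2) = 150 × 0.25 / 0.229 = 163.8.
- Standard error: 1/√(289.2 + 163.8) = 0.0470.

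The number of tests under the Bonferroni correction is not stated, so 10 and 20 are assumed to show a range.

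| Slope on level only | z = slope/0.0470 | Rejects at 0.05 | At 0.05/10 | At 0.05/20 |
|---|---|---|---|---|
| 0.10 | 2.13 | 57% | 25% | 18% |
| 0.15 | 3.19 | 89% | 65% | 57% |
| 0.30 | 6.38 | 100% | 100% | 100% |

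A simulation of the same set-up (300 replicates) also gave 57% and 89% at slopes 0.10 and 0.15, while the RQ x time test rejected in 4.7% and 6.3%. A separate simulation with slope 0.3 (120 replicates) gave 100% for the main effect and 6.7% for RQ x time (8 of 120; exact 95% interval 2.9% to 12.7%).

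**4. The other direction**

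A small simulation (40 replicates) used the same SDs and a separate pre rating in each condition. With RQ slopes of −0.15 before and +0.15 after sharing (change effect 0.30, mean slope zero), the RQ main effect averaged −0.01 and rejected in 5%. With a pure moderation slope of 0.40, time x condition rejected in 7.5% and the RQ main effect in 5%. No planned term picked it up. That layout is not this study's, so these runs show which term targets what and are not power figures.

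**5. Why a three-way term does not fit these data**

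The Procedure section takes the first mood rating before any dialogue, so it belongs to no condition. Code time 0/1 and condition 0 at baseline, −0.5 or +0.5 after a dialogue. Then condition = time x condition in every row, and RQ x condition = RQ x time x condition. The full factorial has 8 columns and rank 6. Dropping the two duplicates leaves intercept, time, condition, RQ, RQ x time and RQ x condition: 6 columns, rank 6. In that model RQ x condition carries 8.3. The same duplication affects the listed time and condition terms: 4 columns, rank 3.

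**The case against.** The strongest defence is that the article condenses a fuller plan. The phrase fixed factors separates fixed from random terms and does not expressly exclude interactions, and the stated purpose for 7.3 is association with mood change. This carries some weight: for 7.3 the authors may intend the interaction and not have written it. It carries less for 8.3, where the article lists what the full model contains and omits any moderation, while naming moderation for 8.1, 8.2 and 8.4.

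A reader might infer three stronger things that the documents do not support.

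- *That the 8.3 model contains RQ and DC in no form.* The sentence before the list says the 7.3 models will be extended, so their main effects can be read as carried over. What is absent is an interaction.
- *That couple clustering will be ignored in 8.3.* The list mentions only a participant intercept, but 8.3 extends 7.3, which extends the Hypothesis 3 model, "including random intercepts for participants nested within dyads". This is an inconsistency to tidy.
- *That false support for 7.3 is near certain.* The 100% rate needs an assumed level slope of about 0.3 SD. At 0.10 SD it is 57% at the nominal 5%, and 18% to 25% under the assumed Bonferroni divisors.

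**Conclusion.** The point holds in this form: as written, the mood models for 7.3 and 8.3 name no interaction with RQ or DC. The 7.3 term estimates association with average mood level, and the 8.3 list has no term for moderation of the condition difference, even with the main effects carried over. This follows from the wording and the model algebra and needs no assumed numbers. A Bonferroni correction lowers the rate of false support but does not redirect the test to the right parameter.

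The rates are illustrative. They rest on assumed variances, an assumed partner correlation and an assumed level slope. The effect is confined to these two confirmatory sub-hypotheses; Hypotheses 1 to 6 do not depend on these terms. The formulas should be settled before the mood data are analysed.

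**What to change.** - **7.3:** add RQ x time and DC x time to the Hypothesis 3 mood model and test those terms.
- **8.3:** model post-dialogue mood (or change from the pre-sharing rating) on baseline mood, condition, RQ, DC, RQ x condition and DC x condition, and test the two moderator x condition terms. Equivalently, in the long-format model, code condition on post-dialogue ratings only and test RQ x condition and DC x condition, leaving out the redundant three-way terms. If a separate pre rating per condition is intended, say which rating serves.
- **Both:** state random intercepts for participants nested within dyads, as for Hypothesis 3.

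The cost is a change of model formula, with no new data or assessments. The interaction tests have less power than the main-effect test they replace, and this should be acknowledged when the results are interpreted.

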Compared to the effects of the co-rumination manipulation on synchrony, mood and appraisal change, we expect that couples’ relationship quality and their dyadic coping strategies have a much stronger effect on synchrony, mood and appraisal change. Couples with a high relationship quality and constructive dyadic coping strategies will already have employed a range of interpersonal emotion regulation and coping strategies to deal with the problem they are discussing, and therefore these brief episodes of natural sharing or co-rumination will minimally affect their synchrony, mood and appraisal changes. In contrast, for couples with a poorer relationship quality or dyadic coping strategies, the co-rumination manipulation to engage in extensively discussing the sharers problems and negative emotions, will have a greater effect on their synchrony and positive mood change than when they engage in their natural way of emotional sharing, but will still result in minimal appraisal changes.

Prior to the emotional sharing task, we will measure a set of variables related to the chronic timescale: relationship quality, dyadic coping and a range of secondary variables (e.g., attachment style, empathy and perceived social support). During the emotional sharing task itself, we will assess phasic processes in the form of movement synchrony [5] and cardiovascular synchrony [20]. Before and after the emotional sharing tasks, we will measure tonic processes: mood and appraisal changes and a range of secondary variables (e.g., conversation experience, perception of partners’ responsiveness and feelings of closeness with the partner).

The proposed experiment has both confirmatory and exploratory parts. The confirmatory part is based on hypotheses that were explicitly derived from the literature on interpersonal emotion regulation. Because of the complexity of the study, we have grouped our hypotheses according to their respective timescales (see Table 1). More detailed information can be found in *Supplementary 1 in*
S1 File*.*

**Table 1 pone.0323526.t001:** Main confirmatory hypotheses for the three timescales.

Timescale	Hypotheses
*Phasic*	1. Relationship partners will display significant levels of movement and cardiovascular synchrony during the emotional sharing tasks, relative to a relevant baseline level of randomized pseudo-interactions. 2. Compared to natural sharing, co-rumination may be associated with enhanced movement and cardiovascular synchrony.

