### Co-rumination manipulation

We will experimentally manipulate the instructions of the emotional sharing task, following a validated procedure developed by Tudder et al (2023) [27]. For half of the sharing episodes, the supporter will receive instructions that promote co-rumination, which involves focusing on a topic, repeatedly discussing the issues, speculating about the antecedents and consequences of the issues, and exploring and unearthing negative emotions. For the other sharing episodes, the supporter will be instructed to respond in a natural way to the sharer. The order of the co-rumination versus natural response will be counterbalanced. Each member of the couple will be instructed once to engage in co-rumination and once to engage naturally with the sharer in all four conditions, the participants will receive digital instructions and physical cards to remind them of their role and the associated instructions.

Before the first sharing episode, participants will be taken by their experimenter to the emotional sharing space with the two armchairs (see Fig 1b), so that they can familiarize themselves with this space Then they will be taken back to their private space, where they will be informed about the first experience to address and be asked to “collect their thoughts” for two minutes. Following this, each participant will again be taken to the emotional sharing space. Participants will then engage in their first round of emotional sharing on the selected experience. After completing the first emotional sharing episode, the participants will go back to the private space and complete the post-dialogue survey about their sharing experience. After completing the first instruction, the instructions for natural sharing and co-rumination will be reversed, and after two rounds, the roles of the sharer and supporter will be switched, and vice versa.

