### Measurement

Table 2 provides a comprehensive overview of the tools and objectives for the measurement employed in this study. More detailed information can be found in Supplementary 2 in S1 File.

**Table 2 pone.0323526.t002:** Overview of the measurement tools, objectives and measurement period.

Timescale	Name	Measurement objectives	Measurement period
*Phasic*	VRMS	Movement synchrony	Emotional sharing episodes
	CMS	Cardiovascular synchrony	Emotional sharing episodes
*Tonic*	BEF	Mood (e.g., *“Helplessness.”)*	Pre-sharing survey and post-dialogue surveys
	ES	Emotional Appraisal (e.g., *“How intense were the negative emotions that you had during this experience?”*)	Pre-sharing survey and post-dialogue surveys
	IOSS	How close the respondent feels with another person (seven images)	Pre-sharing survey and post-dialogue surveys
	SOE	The experiences of partners in conversation (e.g., *“I felt completely like myself during the conversation.”*)	Post-dialogue surveys
	PPR	Individuals’ perceptions of their partners’ responsiveness (e.g., *“My partner understood me.”*)	Post-dialogue surveys
	IER-DSFP	Different interpersonal emotion regulation strategies from partner (e.g., *“My partner tried to get me to talk over and over about what is bothering me.”*)	Post-dialogue surveys
	RQ-ASSC	Relationship quality (e.g., *“My partner and I agreed on how I could best approach the problem.”*)	Post-dialogue surveys
*Chronic*	DCI	Dyadic coping strategies (e.g., *“I tell my partner that it is not that bad and help him/her to see the situation in a different light.”*)	Pre-sharing survey
	PQ-SF	Quality of romantic relationships (e.g., *“He/she takes me in his arms.”*)	Pre-sharing survey
	PSAS-SF	Attachment styles (e.g., *“It helps to turn to my partner in times of need.”*)	Pre-sharing survey
	TAS-20	Alexithymia (e.g., *“I am often confused about what emotion I am feeling.”*)	Pre-sharing survey
	OSRS	Participants’ perception of emotion regulation (e.g., *“I gave someone helpful advice to try to make them feel better.”*)	Pre-sharing survey
	SSL	Perceived social support received (e.g., *“Did you ask for help or advice?”*)	Pre-sharing survey
	SV	Sociodemographic variables (e.g., *“How old are you*.*”*)	Post-sharing survey
	UCLA-LS	Loneliness (e.g., *“I lack companionship.”*)	Post-sharing survey
	IRI	Empathy (e.g., “*I sometimes find it difficult to see things from the other person’s perspective*.”)	Post-sharing survey

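### The covariate plan neither excludes ratings made after each manipulated dialogue nor says that the models without them decide the condition hypotheses

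*Protocol article*

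**What the plan says.** Under Chronic timescale, after calling the Table 1 hypotheses and their analysis techniques the core of the research, the protocol article adds: "we have identified and measured a range of secondary variables that could potentially influence these associations". The next sentence reads: "Our aim is to incorporate these variables as covariates in the analyses to enhance our understanding of the findings". The alpha level and the Bonferroni correction follow directly, and the summary of exploratory analyses comes only after that.

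The section Proposed experiment and hypotheses shows that the secondary variables include measures taken around the dialogues: "Before and after the emotional sharing tasks, we will measure tonic processes: mood and appraisal changes and a range of secondary variables". Its examples are conversation experience and the partner's "responsiveness and feelings of closeness with the partner". Table 2 places SOE, PPR, IER-DSFP and RQ-ASSC in the post-dialogue surveys only, and IOSS both there and in the pre-sharing survey. The Co-rumination manipulation section fixes the order: "After completing the first emotional sharing episode, the participants will go back to the private space and complete the post-dialogue survey".

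Hypothesis 5 in Table 1 expects mood after co-rumination to be as good as, or better than, mood after natural sharing, "possibly due to increased emotional closeness and perceived support".

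**The concern.** Counterbalancing the instruction within couples protects the total effect of co-rumination versus natural sharing. It does not protect an estimate that conditions on something the instruction has already changed. Closeness, responsiveness and support, rated after the dialogue, are what Hypothesis 5 expects co-rumination to raise. A mood contrast that holds them fixed asks how much of the effect is left once its proposed route is blocked, and Hypothesis 5 does not ask that.

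IER-DSFP adds a second problem. Its sample item, "My partner tried to get me to talk over and over about what is bothering me", comes close to describing the co-rumination instruction, so adjusting for it partly adjusts for the condition itself, whatever the outcome.

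Hypothesis 5 is especially exposed because it counts equality as an expected result. An attenuated, non-significant adjusted contrast could be read as support. If adjusted and unadjusted results disagree, the article gives no rule for which one counts.

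**Working it through.** **The plan's own figures.** None bears on this point. The 128 dyads under Sample size determination reproduce (two-sample t-test, d = 0.5, 80% power, two-sided 0.05: 64 per group, 2 × 64 = 128) and are not affected.

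**Step 1: when each secondary variable is rated.** Table 2 lists 15 variables besides the primary ones (movement and cardiovascular synchrony, BEF, ES, DCI, PQ-SF).

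| Timing | Variables | Count |
|---|---|---|
| Only before the task | PSAS-SF, TAS-20, OSRS, SSL | 4 |
| After each dialogue | IOSS (also before), SOE, PPR, IER-DSFP, RQ-ASSC | 5 |
| Once, after all dialogues | SV, UCLA-LS, IRI, DDI, BSRI, MHC | 6 |

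So 5 + 6 = 11 of 15 are rated after a manipulated episode. The six in the last row take one value per person. They cannot shift a within-person contrast in which each person contributes both conditions. The risk to the condition effects therefore lies in the five post-dialogue ratings.

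**Step 2: Hypothesis 5.** Let X be the condition, M a post-dialogue rating and Y mood, with M = aX + error and Y = cX + bM + error. The total effect is c + ab. A model with M as covariate estimates c. If a share p of the total is mediated, c = (1 − p) × total. Hence p = 25% leaves 75% of the effect, p = 50% leaves 50%, and p = 75% leaves 25%.

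**Step 3: check by simulation.** All effect values here are assumptions: total effect 0.50 SD, a = 0.5, 150 dyads (300 people, one episode per condition each), 400 runs. The last column adds an unmeasured episode-level cause of both M and Y, with loading 0.5 on each. Such a cause is plausible because mood and M are rated in the same survey. It raises the slope on M by 0.5 × 0.5 = 0.25, so the adjusted effect should be 0.50 − 0.5 × (p + 0.25) = 0.375 − 0.5p.

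| Share mediated | M left out | M adjusted | M adjusted, shared cause (formula) |
|---|---|---|---|
| 0% | 0.505 | 0.508 | 0.373 (0.375) |
| 25% | 0.499 | 0.375 | 0.253 (0.250) |
| 50% | 0.501 | 0.252 | 0.117 (0.125) |
| 75% | 0.500 | 0.119 | 0.000 (0.000) |
| 100% | 0.496 | −0.005 | −0.138 (−0.125) |

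Leaving M out recovers the total effect throughout; with the shared cause, the unadjusted estimate also stays between 0.493 and 0.503. With a shared cause, adjustment distorts the estimate even when nothing is mediated.

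**Step 4: the other condition hypotheses.**
- Hypothesis 2: synchrony is recorded during the dialogue and the ratings follow, so the ratings cannot mediate it. They may still be consequences of both condition and synchrony. Conditioning on a common consequence creates a spurious association whose sign depends on those two links.
- Hypothesis 6: appraisal is rated in the same post-dialogue surveys. The protocol states no route through closeness here, so the direction is open.
- Hypothesis 8: the interaction with relationship quality or dyadic coping can be distorted if the ratings respond to condition differently across couples. The direction is again open.

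**The case against.** The strongest reply is that the covariate sentence is supplementary. The Phasic and Tonic timescale sections specify the models for Hypotheses 2, 5 and 6 with condition (and time, for mood) as fixed effects and none of these scales. The covariate sentence comes after those models have been called the core, is worded as an aim, and gives better understanding as its purpose. The text after Table 1 assigns the secondary variables to exploratory analyses in almost the same terms. It refers for detail to a supplement that is not at hand, which may list the covariates model by model. The sentence might also refer mainly to chronic measures such as attachment and empathy.

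This reading is plausible, and it narrows the point. It does not remove it. No sentence in the article makes the unadjusted models decisive or excludes the post-dialogue ratings, and the covariate sentence stands before the alpha and Bonferroni rules, ahead of the exploratory summary.

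A reader might also infer more than the documents support:
- *That most secondary variables are the stated mechanism.* The mechanism is hedged and given for Hypothesis 5 only. It is carried mainly by IOSS, PPR and RQ-ASSC.
- *That adjustment removes part of every tested effect.* Removal fits Hypothesis 5. Hypothesis 1 has no condition contrast, and for Hypotheses 2, 6 and 8 the bias has no known sign.
- *That a definite loss of power follows.* With an assumed paired effect of 0.30 halved to 0.15, power at 0.05 falls from 95.5% to 44.7% with 150 pairs, but from 99.9% to 74% with 300 independent pairs. Mood is nested within participants, so dyadic dependence would place the loss between these. Neither the effect nor the share is in the protocol, and the figures ignore the Bonferroni correction and any change in residual variance.

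**Conclusion.** The covariate sentence is wrong as written, and correcting it costs next to nothing. Followed literally, it would let five consequences of the manipulation into the models that test it. For Hypothesis 5 the adjusted contrast would lose whatever part of the effect runs through closeness, responsiveness or support, and a real difference could pass as equality. For Hypotheses 2, 6 and 8 the condition effect could be biased either way.

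The proportional loss for Hypothesis 5 assumes a linear model with no unmeasured common cause of rating and mood; with such a cause the error can be larger. The mediated share is not in the protocol, so the 75%, 50% and 25% remaining are a range of illustrations, not a forecast. The harm arises only if an adjusted model is allowed to decide a hypothesis, which the article leaves open.

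**What to change.** Add to the covariate paragraph under Chronic timescale:
- Hypotheses 2, 5, 6 and 8 are decided by models that contain no variable measured after the manipulation other than the outcome.
- Covariates in confirmatory models are limited to pre-sharing measures (including the pre-sharing IOSS rating), the recorded adherence to the behavioural instructions, and design factors (episode position, role).
- The post-dialogue ratings (IOSS, SOE, PPR, IER-DSFP, RQ-ASSC) are used only as outcomes or in separately labelled exploratory or mediation models.

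The cost is a sentence or two in the analysis plan. Data collection does not change, no data are lost, and adjusted versions can still be reported as exploratory. If the supplement already says this, the article needs only to refer to it at this place.

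### Holm's step-down procedure over the tests of Hypotheses 1–8 would keep the family-wise error of the planned single-step Bonferroni correction and recover a little power, at almost no cost.

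*Protocol article*

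**What the plan says.** The Chronic timescale section of the Data analysis plan sets the level and the correction together. The level is "For all statistical tests α ≤ 0.05 (two-tailed) will be applied". The correction follows two sentences later: "to reduce the likelihood of Type I errors, we will apply the Bonferroni correction to all previously mentioned test results". No number of tests is given.

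The same paragraph says which hypotheses matter most: "The hypotheses presented in Table 1 and the data analysis techniques utilized constitute the core elements of our research". Between that statement and the correction it brings in the secondary variables: "Our aim is to incorporate these variables as covariates in the analyses to enhance our understanding of the findings". The verbal, vocal and facial analyses are described after the correction and are labelled exploratory, as they also are below Table 1.

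Table 1 lists eight hypotheses. Several cover more than one outcome or predictor. Hypothesis 1 reads "Relationship partners will display significant levels of movement and cardiovascular synchrony during the emotional sharing tasks" and Hypothesis 2 reads "Compared to natural sharing, co-rumination may be associated with enhanced movement and cardiovascular synchrony". Hypothesis 7 begins "Higher relationship quality and more constructive dyadic coping strategies will be associated with 1) stronger movement synchrony; 2) stronger cardiovascular synchrony" and continues with mood and appraisal change.

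**The concern.** Single-step Bonferroni holds every test to the same threshold, 0.05 divided by the number of tests, whatever the other tests show. With a confirmatory family of this size, that costs a good deal of power. Holm's procedure tests the smallest p-value at that same threshold and relaxes the threshold after each rejection. It gives the same family-wise guarantee and can only add rejections. At stake is a small number of true effects that would be declared unconfirmed although the 0.05 family-wise error rate allows them to be confirmed. To apply Holm, the family has to be stated, which the present sentence does only by reference to what came before it.

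**Working it through.** **1. Count of tests (inputs from Table 1 and the Phasic, Tonic and Chronic sections).**

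| Hypothesis | Basis | Tests |
|---|---|---|
| 1 | movement, cardiovascular | 2 |
| 2 | movement, cardiovascular | 2 |
| 3 | mood change, roles analysed together ("This approach enables us to examine overall mood changes without splitting sharers and supporters into separate analyses") | 1 |
| 4 | appraisal change | 1 |
| 5 | mood by condition | 1 |
| 6 | appraisal change by condition | 1 |
| 7 | 2 predictors × 4 outcomes | 8 |
| 8 | 2 moderators × 4 outcomes | 8 |
| Total | | 24 |

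The total assumes one score each for appraisal, relationship quality and dyadic coping. The article does not state this, and separate subscale tests would raise the count. Counting numbered hypotheses only gives 8.

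**2. Thresholds.** 0.05/24 = 0.00208 and 0.05/8 = 0.00625, a ratio of 3. With 24 independent tests and no correction, family-wise error would be 1 − 0.95^24 = 0.71. With Bonferroni it is 1 − (1 − 0.05/24)^24 = 0.049. The planned rule therefore does its job.

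**3. The plan's own sample-size figure, reproduced.** For two independent means, effect 0.5, two-sided 0.05 and 64 per group, the noncentral t gives power 0.801, which matches the stated 128 dyads.

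**4. Power after correction.** An effect with 80% power at two-sided 0.05 has mean z = 1.960 + 0.842 = 2.802.
- 24 tests: critical z = 3.078, power = Φ(2.802 − 3.078) = Φ(−0.277) = 0.39.
- 8 tests: critical z = 2.734, power = Φ(2.802 − 2.734) = Φ(0.067) = 0.53.

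On the article's two-group basis with the exact t distribution, power at 0.05/24 is 0.38 with 128 dyads and 0.47 with 150.

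**5. Holm's rule.** Order the p-values p(1) ≤ … ≤ p(24). Compare p(1) with 0.05/24, p(2) with 0.05/23, and so on up to p(24) with 0.05/1, and stop at the first failure. Every threshold is at least 0.05/24, so all Bonferroni rejections are kept. The first step is identical to Bonferroni, so the chance of at least one rejection is the same.

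**6. Size of the gain.** Simulation of 24 normal test statistics with equal correlation 0 or 0.5, mean z of 2.8, 3.24 or 4.0 for the true effects, and 100,000 replicates per setting:

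| True effects among 24 | Gain in average power, Holm over Bonferroni |
|---|---|
| 6 | about 1 to 1.5 points |
| 12 | about 2.5 to 4 points |
| 18 | about 4 to 7 points |

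With 12 true effects, Holm confirmed at least one extra true effect in about 25–36% of simulated studies. Family-wise error stayed below 0.05 for both methods in all these settings. At mean z of about 2.8, average power with 12 true effects rose from about 0.40 to about 0.43.

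**The case against.** The strongest case for leaving the text alone is that Bonferroni is valid, simple and familiar. The gain from Holm is a few percentage points, and Bonferroni has matching simultaneous confidence intervals that Holm lacks in simple form. All of this stands, and it is why the point is minor. It does not make Bonferroni the better decision rule, because Holm never rejects less, and Bonferroni intervals can still be shown alongside.

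Four stronger readings are tempting, and the article does not support them.

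- **That the threshold could vary about tenfold.** This needs a divisor near 80, reached only by assuming a number of secondary-variable or subscale tests that the article does not give. Secondary variables enter as adjustment covariates, and the text below Table 1 places analyses of them under exploratory work. Correction within each hypothesis would also widen the range, but it conflicts with a correction of all the test results. The text supports about 8 to 24 tests, a threefold range.
- **That failing to rank the hypotheses is an error.** Bonferroni over a full family needs no hierarchy. Holm orders tests by p-value and would not supply a ranking either.
- **That the divisor is left open for choice after the data are seen.** The article refers to a supplement, not shown here, for detail on the hypotheses, and a fuller plan may exist. An exact count is the kind of detail an article may leave there, so its absence alone is not a finding.
- **That Holm repairs the power.** The fall from 80% to about 39% is mainly the price of any family-wise correction over 24 tests, and Holm recovers only a small part of it.

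**Conclusion.** The planned correction is valid but can be improved at almost no cost. Over about 24 confirmatory tests, Holm gives the same family-wise control under any dependence, with average power higher by about 1 to 1.5, 2.5 to 4 or 4 to 7 points when 6, 12 or 18 effects are true. Power to find at least one effect does not change, and the 80% used for planning is not restored. Severity is minor.

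The size rests on three assumptions: one score per construct (hence 24 tests), equal correlation of 0 or 0.5 between tests, and true effects with mean z between 2.8 and 4.0. The 0.38 and 0.47 figures follow the article's comparison of independent groups. Every couple takes part in both conditions, so power for the within-couple contrasts would differ and depends on a correlation that the article does not give. The validity of Holm and its advantage over Bonferroni do not depend on any of these assumptions.

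**What to change.** Replace the Bonferroni sentence with:

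> Family-wise error is controlled at two-sided 0.05 with Holm's step-down procedure over the tests of H1–H8 in Table 1 (24 tests if each construct is scored as one total; the count is fixed before analysis if subscales are used). Coefficients of secondary covariates and the verbal, vocal and facial analyses are outside this family and exploratory.

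The change is to wording only and needs no new data. Its costs are that Holm has no simple matching simultaneous confidence intervals, for which Bonferroni intervals can still be reported, and that findings on secondary variables cannot be presented as confirmed.
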